## Abstract

**Background:**

The current literature suggests that forming implementation intentions (simple ‘if-then’ plans) about how to refuse the offer of a cigarette may be an effective intervention to reduce smoking initiation in adolescents. This study is a pragmatic trial to test the effectiveness and cost-effectiveness of such an intervention in reducing smoking initiation in a sample of UK adolescents.

**Methods/Design:**

A cluster randomised controlled trial with at least 36 schools randomised to receive an implementation intention intervention targeting reducing smoking initiation (intervention group) or increasing homework (control group). Interventions will be conducted at the classroom level and be repeated every six months for four years (eight interventions). Objectively assessed (carbon monoxide monitor) and self-reported smoking plus smoking related cognitions (e.g., smoking intentions, attitudes, norms and self-efficacy) will be assessed at baseline and 12, 24, 36 and 48 months post baseline. Objectively assessed smoking at 48 months post baseline will be the primary outcome variable. Health economic analyses will assess life years gained.

**Discussion:**

The results of the trial will provide information on the impact of a repeated implementation intention for refusing offers of cigarettes on rates of smoking initiation in adolescents.

**Trial registration:**

ISRCTN27596806

## Background

Both in the UK and internationally, tobacco smoking continues to be an important cause of morbidity and mortality. For example, smoking related illnesses are estimated to kill over 100,000 people in the UK each year [1,2], usually later in life. Yet smoking is a behaviour that is, in general, taken up between the ages of 10 and 20 years. A variety of different research studies have supported the idea that the vast majority of smokers take up this habit as adolescents [3-5] with 40% of adult smokers having started before they reached 16 years of age [1]. The General Household Survey [6] reported that 38% of adult regular smokers took up the habit before the age of 15 years. This appears to be the case despite the fact that health promotion messages have ensured that awareness of the health consequences of smoking is now widespread, even among the young. In the UK, while the rates of regular smoking at 11 years of age are only 0.5%, this rapidly rises to 15% by 15 years of age, and then more gradually to around 20% among young adults [7]. The recent UK Department of Health [2] plan is to reduce the rates of regular smoking in 15 year olds to 12% or less by the end of 2015. Two important ways to tackle smoking-related harm are interventions to help individuals (usually adults) quit smoking and interventions to help individuals (usually adolescents) not to initiate smoking. The present paper reports the protocol for an intervention designed to reduce smoking initiation in adolescents as potentially the most effective way to reduce smoking-related harm.

A worthwhile intervention to reduce smoking initiation in the groups most likely to take up this habit (i.e., adolescents) would need to have at least three important characteristics: strong effects on reducing initiation; wide reach; and low cost. Promising initial data have been collected [8] (i.e., an explanatory trial) on the efficacy of one intervention technique that may have all of these characteristics. The study outlined here would aim to collect further data on the outcome effectiveness and cost-effectiveness of this technique in the form of a cluster randomised controlled trial (i.e., a pragmatic trial). Given the nature of the existing data in this area, this has been cast as a pragmatic trial [9] that could inform the potential roll out of this intervention for widespread use. The intervention in question is the formation of *repeated implementation intentions* about how to refuse offers of cigarettes. Implementation intentions are simple ‘if-then’ plans [10] about how to respond to environmental cues in order to help achieve a goal such as not taking up smoking, e.g., If offered a cigarette I will say ‘no thanks, I don’t smoke’. Such plans can be formed before the opportunity to act presents itself and have been found to be an effective means to change a range of behaviours [11]. Our research has shown that the repeated formation of implementation intentions about how to refuse offers of cigarettes can have a strong effect on reducing smoking initiation rates among adolescents [8,12]. In addition, this is a simple intervention that could be deployed across most schools (i.e., has wide reach) in order to help tackle smoking initiation in adolescent groups. Finally, this intervention is relatively low cost, requiring around 30 minutes per session to implement (including anti-smoking messages and completing an implementation intention questionnaire). Such an intervention could offer ‘value for money’ and be rolled out to significant proportions of the adolescent population in the UK.

Adolescence is the period during which the vast majority of smokers take up this habit in the UK [1,3]. As such it represents a key period during which to intervene. A considerable number of interventions have been tested in this age group. The vast majority of such interventions have been school-based but have met with only mixed evidence of effectiveness (for reviews see [13,14]). In part this may be attributable to lack of thorough evaluation. Nevertheless, even among high quality randomised controlled trials of school-based interventions the evidence is mixed. For example, information-based interventions have generally been ineffective, while social influence interventions have tended to show rather mixed effectiveness [13]. The most highly regarded and longest trial of this type of intervention was the Hutchinson Smoking Prevention Project which reported no evidence for effectiveness over a period of 8 years [15]. The ASSIST project is another well conducted trial carried out in the UK to evaluate a peer-led intervention to reduce smoking initiation [16]. This RCT did report support for a peer-led intervention over both a one- and a two-year period. More mixed evidence has been reported for interventions that target social competence or test multi-modal interventions [13], although there are far fewer such studies in this area. A further problem has been that many of these interventions have been quite intensive and costly to implement. For example, the Hutchinson Smoking Prevention Project [15] included a total of 65 lessons provided over a period of 8 years. Similarly, the ASSIST intervention involved two-day training events for the peer supporters. Such interventions may be costly and difficult to scale up into population level interventions that could be conducted in all schools across the UK at reasonable cost and with relative ease. In contrast, an intervention involving forming a repeated implementation intention about how to refuse offers of cigarettes would appear to be efficacious in reducing smoking initiation rates [8,12] and is also simple, easy to administer, cheap, and would appear to have the potential to be readily scalable up into a population-level intervention delivered in the vast majority of UK classrooms.

Gollwitzer [10] has defined an implementation intention as a plan of how, where and when to commit a behaviour (see [11] for a review). This type of plan establishes an ‘if-then’ link between a situation and a planned behaviour (e.g., between the offer of a first cigarette and a refusal strategy). Implementation intentions have proved to be effective yet simple means of changing a range of different health behaviours [17]. Gollwitzer and Sheeran’s [11] meta-analysis showed that across 94 independent studies in both laboratory and field settings, implementation intentions had an average effect size of d+ = 0.65, although only 6 out of the 94 studies reviewed by Gollwitzer and Sheeran [11] investigated health-risk behaviours and none examined smoking. More recently, research has begun to emerge to suggest that implementation intentions may be effective in promoting smoking cessation. For example, in two field experiments, Armitage [18,19] found that implementation intentions caused significantly more smokers to quit (up to 19% quit) compared with smokers randomly allocated to active control conditions (2% quit), suggesting that the technique has utility in this domain.

Implementation intentions have also been used in relation to reducing smoking initiation. Two studies have assessed the impact of forming an implementation intention about what to say to refuse the offer of a cigarette on subsequent smoking initiation. Higgins & Conner [12] reported that among adolescents who formed such an implementation intention (on a single occasion) 0% went on to initiate smoking in the next two months, whereas 6% did so in a control condition. Conner & Higgins [8] more recently reported the results of an explanatory cluster randomised controlled trial of repeated implementation intentions in a more appropriately powered study. Classes of children were randomly allocated to complete implementation intentions about how to refuse offers of cigarettes (intervention) or complete their homework (control) on 7 occasions between the ages of 11–12 and 13–14 years (both groups also read simple anti-smoking messages on each occasion). Research assistants delivered the intervention in classroom time to whole classrooms of children in approximately 30 minute sessions. After controlling for various known predictors of smoking initiation (e.g., gender, attitudes to smoking, friends and family smoking) and the multi-level nature of the data, rates of self-reported and objectively assessed smoking at age 15–16 years were significantly lower in the intervention compared to the control condition (d+ = 0.24 and 1.04 for self-reported smoking and objectively assessed smoking respectively). For self-reported smoking, the unadjusted reduction in smoking initiation was approximately 7% between the intervention and control conditions, while the unadjusted difference for objectively assessed smoking was approximately 10%.

### Research questions

The following research questions will be addressed in this trial:

• Can repeated implementation intentions related to refusing offers of cigarettes reduce smoking initiation rates in 11–16 year olds relative to a control group of adolescents?

• What is the cost effectiveness of such an intervention?

## Methods/Design

### Design

This study will use a pragmatic cluster randomised controlled trial design (see Figure 1). The unit of randomisation will be schools. Individual adolescents will be the unit of analysis although we will take account of clustering by schools.

**Figure 1 F1:**
[figure not shown]
Flow Chart of Study Procedures for both Groups.

### Sampling and recruitment of schools and adolescents

All secondary schools (except independent schools) in the Leeds and Staffordshire areas will be invited to take part. There will be a total of at least 36 schools recruited into the RCT (see Figure 2). We will approach secondary schools in the West Yorkshire and Staffordshire Local Education Authorities (the participating regions) and the surrounding areas to request participation in the proposed research. Through previous work and that of our collaborators we have good experience of recruiting and working with schools in both regions. Based on our previous work [8,12] we anticipate at least 50% of schools will agree to participate. Within each school all available classes in year 7 (11–12 year olds) will participate (estimated to be at least 4 classes of 30 adolescents per school).

**Figure 2 F2:**
[figure not shown]
Randomization flow chart.

We will ask head teachers to sign a written consent form agreeing that their schools take part in the trial and agreeing not to introduce any new anti-smoking interventions during the time period of the trial without informing the trial staff. We will seek to record carefully any anti-smoking initiatives conducted in each school during the trial period. Through the schools we will seek to obtain parental consent (an opt-out procedure) for participation in the RCT (intervention plus data collection) through letters from the participating schools.

### Study population

#### Proposed sample size

In selecting a sample size we have based our estimates on six factors: 1) the size of effect observed in our previous research; 2) the fact that school will be the unit of randomisation and adolescents will be clustered within schools; 3) a likely dropout rate based on our previous research; 4) an estimate of the intra-class correlation coefficient (ICC); 5) choice of significance level at 5% and sought power of at least 90%; and 6) a correction for imbalances in recruitment or drop-out rates across schools. Based on these values we have estimated the power of our study to detect differences between intervention and control arms of the RCT using our proposed sample sizes. In relation to effect size, our explanatory trial [8] indicated that the intervention reduced objectively assessed smoking rates from around 14% to around 4% (in unadjusted data) in 15–16 year olds. In the analysis controlling for other predictors of smoking and the multilevel nature of the data (children clustered within classes, classes clustered within schools) this equated to a large effect size with an odds ratio of 0.15 (95%CI: 0.03–0.80). We have conservatively powered the present study using a value at the upper end of this range, i.e., to detect a difference of 5% between the intervention (9% rate of smoking initiation) and control (14% rate of smoking initiation) arms at the end of the study (i.e., equivalent to an odds ratio of 0.61). In relation to dropout rates we have estimated that 85% of those who begin the study will be available to follow-up at 48 months [8]. For ICC we have estimated a value of 0.01 based on previous research [8]. In relation to significance level we have used an alpha of 0.05 using a two-sided test in order to be open to testing the possibility that the intervention actually increased smoking initiation rates. In relation to a correction factor to allow for imbalances in recruitment or dropout we estimate this will not reduce our statistical power by more than 1%.

Using these assumptions we have estimated that we require a total of 36 schools with 18 randomly allocated to the intervention arm and 18 to the control arm of the RCT. Within each school, we estimate that we need to approach at least 120 adolescents at baseline (approximately 4 classes per school). Based on an 85% recruitment rate (due to refusal to participate and non-attendance on testing days) the overall number of adolescents available for analysis will be: 0.85 * 18 * 120 = 1836 per group. The effective number of adolescents per group will be reduced further due to a design effect (i.e., adolescents clustered by school): Design effect = 1 + (m – 1)*ICC, where m is the number of participants per cluster. This yields a design effect of 2.01 and reduces the effective sample size per group to 913 (1836/2.01). This effective sample size yields a statistical power of 90.65% to detect a 5% difference in smoking initiation between the intervention (9% initiation) and control (14% initiation) arms using a two-sided test with an alpha of 0.05. Adding our correction factor for potential imbalances in recruitment would still provide a power of almost 90%. Therefore our proposed sample size is 4320 adolescents from 36 schools (18 intervention; 18 control), with approximately 120 adolescents being approached per school.

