### Randomisation

The unit of randomisation will be schools and our sample size calculations and analyses takes account of this clustering of the data. We believe randomising by school before the intervention begins is most appropriate in order to reduce the likelihood of contamination between the intervention and control conditions (randomising by individual or classroom risks such contamination). The Trial Statistician (RW) will use a random number generator to randomly allocate schools to the control or intervention arms of the trial. Schools have requested feedback on which condition they are randomised to before giving final agreement to participate and agreeing to send out letters to parents. The trial will therefore deviate from best practice in recruiting children to the trial after rather than before randomisation. We will monitor any consequential effects on participation rates. As we hope to recruit all classes in a school year movement between classes within a school should not be a problem. However, adolescents moving school during the RCT are likely to have missing data. Of those initially participating in the study at age 11–12 years we anticipate a cumulative loss to follow-up at age 15–16 years of 15% (based on our previous research, [8]). We will make efforts to minimize drop out (e.g., attempting to ensure each school is visited on more than one day to collect smoking measures) and any potential biases attributable to drop out will be explored statistically.

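### The sample size assumes two separate 15% losses but applies only one, so the 90.65% power does not follow from the protocol's own assumptions

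*Protocol article*

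**What the plan says.** All of the sample-size inputs are in the protocol article under Proposed sample size.

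- **Target:** "choice of significance level at 5% and sought power of at least 90" percent.
- **Test:** "we have used an alpha of 0.05 using a two-sided test".
- **Effect:** "to detect a difference of 5% between the intervention (9% rate of smoking initiation) and control (14% rate of smoking initiation) arms".
- **Clustering:** "For ICC we have estimated a value of 0.01 based on previous research", with 18 schools per arm and 120 adolescents approached in each.
- **Dropout:** "In relation to dropout rates we have estimated that 85% of those who begin the study will be available to follow-up at 48 months". The Randomisation section repeats this for initial participants: "we anticipate a cumulative loss to follow-up at age" 15–16 years, put at 15%.
- **Recruitment:** "Based on an 85% recruitment rate (due to refusal to participate and non-attendance on testing days) the overall number of adolescents available for analysis" is then given as 1836 per group.

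From 1836 the section takes a design effect of 2.01 and an effective size of 913 per group, and concludes: "This effective sample size yields a statistical power of 90.65% to detect a 5% difference in smoking initiation". It allows up to one further point of power for imbalance between schools and describes what remains as close to 90%. The total of 4320 is the number approached.

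**The concern.** The two 85% figures have different denominators. The recruitment figure applies to children approached and removes those who refuse or are absent. The dropout figure applies to children who have begun and removes those lost over four years. A child has to pass both to supply a 48-month outcome, so the two should be multiplied. The calculation uses one, calls it recruitment, and presents the result as the number for analysis.

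The primary outcome is measured at 48 months, which is where the omitted loss falls. If both losses occur as assumed, the number of children with an observed primary outcome is 15% below the stated figure, and power is below both the published value and the protocol's own target. Readers will use that published power to interpret a null result.

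**Working it through.** **Inputs** (all from Proposed sample size): control 14%, intervention 9%, two-sided alpha 0.05, ICC 0.01, 18 schools per arm, 120 approached per school, 85% recruited of those approached, 85% retained of those who begin.

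**Formulas.** With m children per school:

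- design effect DE = 1 + (m − 1) × ICC
- effective size per arm n = 18m / DE
- power = Φ{ [d − 1/n − 1.96 √(2p̄(1 − p̄)/n)] / √([p₁(1 − p₁) + p₂(1 − p₂)]/n) }

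Here d = 0.05, p̄ = 0.115, 2p̄(1 − p̄) = 0.20355 and p₁(1 − p₁) + p₂(1 − p₂) = 0.1204 + 0.0819 = 0.2023. The 1/n term is the continuity correction.

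**Step 1: reproduce the protocol (one loss).**

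- m = 0.85 × 120 = 102, so 18 × 102 = 1836 per arm
- DE = 1 + 101 × 0.01 = 2.01, so n = 1836 / 2.01 = 913
- power = Φ[(0.05 − 0.00110 − 0.02927) / 0.01489] = Φ(1.319) = 90.65%

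This matches exactly, so the protocol used the continuity-corrected formula. Without the correction the same n gives 91.8%.

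**Step 2: apply both stated losses.**

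- m = 0.85 × 0.85 × 120 = 86.7, so 18 × 86.7 = 1560.6, about 1561 per arm
- DE = 1 + 85.7 × 0.01 = 1.857, so n = 1560.6 / 1.857 = 840
- power = Φ[(0.05 − 0.00119 − 0.03050) / 0.01552] = Φ(1.180) = 88.1%

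| | One loss (as published) | Both losses |
|---|---|---|
| Per school | 102 | 86.7 |
| Per arm | 1836 | 1561 |
| Design effect | 2.01 | 1.857 |
| Effective size per arm | 913 | 840 |
| Power, continuity-corrected | 90.65% | 88.1% |
| Power, uncorrected | 91.8% | 89.6% |

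The effective size needed for 90% power is 893 per arm with the correction and 854 without; 840 reaches neither. Taking off the protocol's own imbalance allowance of up to one point leaves about 87%. Power falls by less than a 15% loss might suggest because smaller clusters also lower the design effect.

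**Step 3: look for a hidden allowance.** 36 × 120 = 4320 exactly, so the total contains no inflation for dropout. The expected flow is 4320 approached, 0.85 × 4320 = 3672 at baseline, and 0.85 × 3672 = 3121 at 48 months.

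**Step 4: how much would imputation have to recover?** For 90% power at 18 schools per arm, solve 18m / (0.99 + 0.01m) = 893, which gives m = 97.5. As a rough guide, treating recovered information as extra children per school, imputation would have to restore (97.5 − 86.7) / (102 − 86.7) = 10.8 / 15.3, or about 70%, of the outcome information lost to dropout.

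**The case against.** There are three serious arguments on the other side.

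**There may be only one loss, mislabelled.** The six listed factors include dropout but no recruitment rate, and the calculation claims to use the assumptions just listed. Absence on testing days could also describe follow-up loss: the Randomisation section proposes visiting schools on more than one day to limit dropout. On this reading 1836 and 90.65% stand. However, the calculation calls its 85% a recruitment rate and attributes it partly to refusal, and a child who refuses has not begun. The reading also requires all 120 children approached in every school to start. Yet parents may opt out, children may decline the measures, and those missing at baseline are excluded from the intention-to-treat analysis. The text would still need correcting, and a loss it names would have no allowance.

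**Multiple imputation keeps everyone with baseline data.** If 15% are not recruited, 1836 per arm may correctly describe the nominal analysis set. This part stands. It does not rescue the power, because imputing from baseline does not in general restore the information in an unobserved outcome, and Rubin's rules carry that uncertainty into the variance. The protocol itself lists dropout as a sample-size input.

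**The effect is small and the inputs are minimums.** This also stands. The drop is about 2.5 points, and the protocol speaks of at least 36 schools and at least 120 adolescents in each. Larger numbers could make up the shortfall, but the stated power is for exactly 36 and 120.

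**Conclusion.** The point holds: the power is wrong as written. Under the protocol's own two assumptions, about 1561 rather than 1836 adolescents per arm would have an observed 48-month outcome. Power is then 88.1% by the formula the protocol used, or 89.6% without the continuity correction. Both are under the 90% sought, before any imbalance allowance.

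This rests on the two losses being distinct, as their wording says, and on imputation recovering little of the missing outcome information. Power would return to 90.65% only if imputation recovered all of it. The design is not seriously underpowered. The fault is that the headline number and power do not follow from the stated inputs.

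**What to change.** Restate the calculation under Proposed sample size with both losses: 86.7 adolescents per school with 48-month data, about 1561 per arm, design effect 1.857, effective size 840, power about 88%, and about 87% after the imbalance allowance. Report separately the numbers approached (4320), expected at baseline (about 3670) and expected with 48-month data (about 3120). Remove the 90.65% figure and the statement that power stays close to 90% after the correction. Say that 1836 per arm is the expected baseline sample, which imputation retains in the analysis.

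If the authors intended only one loss, they should say which one, correct the label, and explain why the other needs no allowance.

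The cost is a rewording and a slightly less favourable stated power. Correcting the record does not require more schools. If the 90% target is to be kept with both losses, the same formula gives 89.8% with 19 schools per arm and 91.3% with 20. Alternatively, about 135 adolescents approached in each of 36 schools gives an effective size of 893 and 90% power. These figures are before the imbalance allowance.
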